##### BWW utilization data

BWW will provide a report of each participants’ use at 2 time points during the study: 1) after all participants have been enrolled for 3 months, and 2) study end. This will include total number of logins, average and total time on the site, along with logs of activity such as pages viewed and posts made.

##### BWW satisfaction

At the end of the BWW access period (month 3 for ITG, month 6 for DTG) participants will be asked to rate BWW overall and indicate if they would recommend it, pay for it, and continue to use it if available.

#### Outcome measures

##### Primary and secondary outcomes

The primary outcome is the total score on the Recovery Assessment Scale-revised (RAS-r) at 3 months. The RAS-r is a 24-item validated pan-diagnostic consumer-oriented outcome measure [31]. All items are scored on a 5-point scale from ‘strongly disagree’ to ‘strongly agree.’ The choice of the RAS-r reflects the current “recovery era” for mental health policy and services and the increasing focus on consumer achievement of satisfying and fulfilling lives, rather than being symptom free [31]. Secondary outcomes include the five subscale scores of the RAS-r: 1) personal confidence and hope, 2) willingness to ask for help, 3) goal and success orientation, 4) reliance on others, and 5) not dominated by symptoms; symptoms of depression and anxiety measured with the Personal Health Questionnaire-9 item (PHQ-9) and the Generalized Anxiety Disorder Questionnaire-7 item (GAD-7) respectively; quality of life measured with the EuroQOL group’s EQ-5D-5 L [32]; and community integration assessed with the Community Integration Questionnaire (CIQ) [33]. The 15-item CIQ is a brief, reliable measure of a person’s level of integration into the home and community. The overall score ranges from 0 to 29 with a higher score indicating better integration. The CIQ can also be divided into 3 subscales: 1) home integration, 2) social integration, and 3) productivity [33]. Timing of the completion of outcome assessments is outlined in Table 1.

**Table 1 Tab1:** Timing of outcome assessments

Measures/Assessments	Baseline	3 months	6 months
RAS-r	X	X	X
PHQ-9	X	X	X
GAD-7	X	X	X
CIQ	X	X	X
EQ-5D-5 L	X	X	X
Adapted CSRI^a^	X	X	X
Out-of-pocket costs^b^	X	X	X
Health Administrative Data	N/A	X	X
BWW satisfaction	N/A	X (ITG)	X (DTG)

*RAS-r* recovery assessment scale-revised, *PHQ-9* personal health questionnaire, 9-item, *GAD-7* generalized anxiety disorder questionnaire, 7-item, *CIQ* community integration questionnaire, *EQ-5D-5 L* Euro-QOL quality of life measure, *CSRI* client service receipt inventory, *BWW* big white wall, *ITG* immediate treatment group, *DTG* delayed treatment group, *N/A* not assessed

^a^Adapted for the Ontario health care context

^b^Includes costs for medication, laboratory investigations, mental health services, and physical health services

##### Health care utilization and costs

Self-reported health care utilization will be assessed with the Client Service Receipt Inventory [34], adapted for the Ontario context. This measure captures utilization of physician and hospital services as well as community mental health services. Health administrative data will be used to validate reports of physician and hospital care, however, community service use and non-physician visits are not captured in Ontario data. Studies of reliability of self-report data over a 3 month recall period demonstrate approximately 60 % exact match with roughly equal proportions of over and under-reporting [35]. High emotional distress may be associated with over-reporting, and hospital and ED use is typically more accurately self-reported than outpatient care [35]. The CSRI will also assess prescribed medication and adherence. Self-reported out-of-pocket costs for medication, laboratory investigations, mental health services, and physical health services will be captured using validated questions from the Commonwealth Fund Survey of patients with Complex Needs [36].

Health administrative data will be retrieved after study completion from the Institute for Clinical Evaluative Sciences (ICES), a not-for-profit research institute encompassing a secure and accessible array of Ontario's health-related data. At ICES, individual-level health care and socio-demographic data from various sources are de-coded and linked using an encrypted health care number (ICES Key Number). We will extract individual data on inpatient, ED, outpatient health care utilization, as well as prescription drug costs (for people on social assistance or over age 65) during the study period and link to individual survey data using encrypted OHIP identifiers created by ICES authorized personnel. Individual health care costs will be determined using methods developed for use with Ontario data [37].

We will track incremental costs associated with BWW using unit prices from expenditures related to its use (capital and operating costs such as license fees) as well as human resources required to support its implementation.

#### Adverse events

There is a growing consensus that adverse events (AEs) need to be evaluated in behavioural intervention trials [38, 39], as there is a theoretical risk of deterioration, especially if online self-help tools are misunderstood or not properly applied [38]. We will compare pre-defined AEs (see Table 2) between the ITG and DTG participants at 3 months, and the ITG-e and ITG-n participants at 6 months for clinically important differences that may be a result of BWW. Moreover, an independent data safety and monitoring board (DSMB) comprised of three content and methodology experts assembled for this trial will review available AE data at two interim time points: after the first 150 participants have completed 3 months, and again after 500 participants have completed 3 months, to determine if any investigation is required and if the trial is safe to continue. Health administrative data will not be available within this timeframe and will not be reviewed by the DSMB. DSMB terms of reference are available from the study investigators.

**Table 2 Tab2:** Adverse Events

Adverse Event	Measure	Description
Mental health Hospitalization	CSRI; Health administrative data	Number of hospitalizations on a psychiatric unit
Mental health ED visit	CSRI; Health administrative data	Number of ED visits for a mental health reason
Crisis service use	CSRI	Number of times using crisis supports
Increased suicidal ideation	PHQ-9 item 9	Increase in PHQ-9 item 9 score
Death	Health administrative data	All-cause mortality
Worsening depression or anxiety	PHQ-9, GAD-7	Increase in PHQ-9 or GAD-7 score over the prior 3 months
Declining social and community integration	CIQ	Decrease in CIQ score over the prior 3 months
Worsening disability	EQ-5D-5 L	Decrease in EQ-5D-5L scores over the prior 3 months
Medication discontinuation	Author question added to CSRI	Self-reported discontinuation of psychotropic medication without provider knowledge

*CSRI* client service receipt inventory, *PHQ-9* personal health questionnaire, 9-item, *GAD-7* generalized anxiety disorder questionanire, 7-item, *CIQ* community integration questionnaire, *EQ-5D-5 L* Euro-QOL quality of life measure

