### Part 1. Pragmatic randomized controlled trial

#### Recruitment

Participants will be recruited at a number of entry or exit points including outpatient clinics and their waitlists, emergency department (ED) discharges, and rapid assessment clinic discharges. Outpatient clinics include youth mental health services (age 16 and over only), adult general psychiatry consultation services (typically serving mood and anxiety disorders), psychotherapy services, post-traumatic stress and trauma therapy services, an outpatient substance use program, and a borderline personality disorder clinic. These recruitment settings were selected because: 1) they serve patients with the potential to benefit from the intervention, 2) they were identified by the participating sites and OTN as high priority settings, and 3) they have high volumes of use and turnover that will allow the implementation organization to reach their recruitment target. With the exception of the ED and rapid assessment clinics, the wait times to access these services vary from 4 months up to 2 years. Participation in the study will not affect wait list position or access to services.

Potential participants will be approached by a member of the clinical staff either by telephone, or in person in the clinic or ED. Hard-copy pamphlets or a website link to the study information will be provided. Once a potential participant indicates their interest, a research assistant (RA) or research co-ordinator (RC) will either meet them in person or contact via telephone to provide more information and obtain consent. Consent will include: 1) Consent to participate in the RCT (required), 2) Consent to be contacted for a qualitative interview (optional), 3) Consent to provide individual provincial health insurance plan (OHIP) number for linkage of survey data to health administrative data (optional), and 4) Consent for primary care provider to be notified of study enrollment (optional).

Separate consent to be re-randomized at 3 months will be obtained from ITG participants who opt-in to the nested intervention extension arm of the trial. This will be done with a question posed at the end of the 3 month data collection survey.

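### Table 2 counts hospitalizations by ward rather than by reason and has no self-harm row, so overdose or self-harm admissions spent entirely off a psychiatric unit are left out of the hospitalization comparison

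*Protocol article*

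**What the plan says.** The Adverse events section sets out nine pre-defined events in Table 2 and makes them the basis of the safety comparison: "We will compare pre-defined AEs (see Table 2) between the ITG and DTG participants at 3 months". The same comparison is repeated at 6 months between the extension and no-extension groups.

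The hospitalization row is labelled as a mental health event and described as "Number of hospitalizations on a psychiatric unit". The ED row beneath it is described as "Number of ED visits for a mental health reason". Both list the CSRI and health administrative data as sources. The row nearest to self-harm concerns suicidal ideation and is scored as "Increase in PHQ-9 item 9 score". Fatal events come under "All-cause mortality", from administrative data only.

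Wider hospital use is collected elsewhere. Under Health care utilization and costs, the article says of the CSRI: "This measure captures utilization of physician and hospital services as well as community mental health services". Of the administrative data it says: "We will extract individual data on inpatient, ED, outpatient health care utilization". Both are presented as utilization and cost data, not as adverse events. The safety board reviews adverse event data twice, after 150 and after 500 participants have completed 3 months, and does not see administrative data at either review.

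**The concern.** The label and the definition of the hospitalization row do not match. The label refers to the nature of the admission; the definition refers to the ward. Two adjacent rows with the same sources therefore follow different rules, and a serious event can satisfy the label without satisfying the definition.

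The population makes this worth settling. There are no exclusion criteria. Recruitment covers ED discharges and outpatient clinics that include "an outpatient substance use program, and a borderline personality disorder clinic". One site is a community general hospital whose ED sees many mental health-related visits. The article does not say how often participants in these settings are admitted to non-psychiatric beds after overdose or self-harm, but it gives no reason to treat that route as closed.

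At stake is the content of the safety comparison. Self-harm serious enough for admission is an outcome that a reader would expect a mental health hospitalization count to include. The primary and secondary efficacy outcomes are not affected.

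**Working it through.** No stated figure bears on this point, so the check is textual. Take one case: an admission for overdose or self-harm that begins and ends on a medical, surgical or intensive-care unit. Put it through each row of Table 2.

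| Table 2 row | What triggers it | Does the admission count? |
|---|---|---|
| Hospitalization | Stay on a psychiatric unit | No |
| ED visit | Visit for a mental health reason | Possibly, if the patient came through the ED and the visit is classed that way; counted as a visit, not an admission |
| Crisis service use | Use of crisis supports | Only if separately used |
| Suicidal ideation | Rise in one PHQ-9 item | Ideation only, and only if the score rose |
| Death | All-cause | Only if fatal |
| Depression or anxiety worsening | PHQ-9 or GAD-7 rise | Not the event itself |
| Integration decline | CIQ fall | Not the event itself |
| Disability worsening | EQ-5D-5L fall | Not the event itself |
| Medication discontinuation | Self-report | No |

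Of the nine rows, one concerns hospitalization and it is restricted to psychiatric units. None names self-harm, overdose or a suicide attempt.

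The next question is whether another section widens the definition.

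- **Health care utilization and costs:** covers hospital use through the CSRI and inpatient administrative data with no stated ward restriction, but does not turn it into an adverse event.
- **Primary and secondary analyses:** describes CSRI utilization at baseline and 3 months and reports adverse events descriptively. It leaves the Table 2 definitions as they are.
- **Data analysis:** administrative data are analysed only after study end. Until then the hospitalization row rests on the CSRI alone.

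Varying the case shows where the gap closes. If the patient later moves to a psychiatric unit, that later stay counts. If the patient dies, the death counts. If the patient arrives through the ED, the ED row may count the visit, but nothing there separates it from any other mental health visit. What remains outside the hospitalization comparison is the admission spent entirely off a psychiatric unit.

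**The case against.** The strongest reply is that the unit rule is a deliberate and workable choice. Participants can readily recall whether they were on a psychiatric unit, whereas attributing a medical admission to a mental health cause from self-report takes judgement. The rule is the same in both arms, adverse events are to be reported descriptively, and neighbouring rows pick up part of what is missed. The article is also a condensed source: neither the adapted CSRI items nor the safety board's terms of reference are shown.

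Much of this stands, and it limits the point. It does not remove it, because the definition is printed in the article and the arms are to be compared on it. Ease of recall explains a ward-based question to participants. It does not explain using a ward rule with administrative data, when the ED row already applies a reason rule to the same two sources.

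Three stronger readings are tempting and are not supported:

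- **That such events disappear from the safety data.** They may be counted as ED visits, as a later psychiatric stay or as deaths, and hospital use is collected as utilization. The loss is of classification and severity within the adverse event comparison.
- **That the comparison is biased between arms.** Nothing in the article suggests that the rule misses more events in one arm than in the other.
- **That the under-count can be sized.** Suppose 1 to 3 % of 1000 participants had such an admission, 30 to 60 % of these were off a psychiatric unit, and 3 to 5 % of participants (30 to 50 events) had a psychiatric-unit stay. Then 1000 × 0.01 × 0.30 = 3 to 1000 × 0.03 × 0.60 = 18 admissions would be missed, or 3/(3 + 50) = 6 % to 18/(18 + 30) = 38 % of the total. Every rate is assumed, the ends of the range pair opposite extremes, and the plan's own 30 % attrition is ignored. It shows the arithmetic and is not an estimate.

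**Conclusion.** The point holds as a gap in one event definition. As written, the between-arm hospitalization comparison leaves out an overdose or self-harm admission spent wholly on a non-psychiatric unit, and no row of Table 2 identifies self-harm. This follows from the wording alone and depends on no assumed rate. Its size cannot be estimated from the article.

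This is an inexpensive improvement to safety ascertainment, not a flaw that undermines the trial. The conclusion assumes that the Table 2 wording governs how events are counted. If the adapted CSRI or a coding manual that is not shown already records the reason for admission on any unit, what remains is to reconcile Table 2 with it.

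**What to change.** **End-of-study comparison.** Define the row as hospitalizations for a mental health, substance use or self-harm reason, on any unit, from the inpatient administrative data already being extracted. Report psychiatric-unit stays as a subset, so the existing definition is preserved. Report self-harm-related ED visits and admissions separately. This needs a coding rule written before the data are examined, and confirmation that the extract carries a reason or diagnosis for inpatient stays. The article does not say so, although the ED row presupposes that a reason is available for ED visits.

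**Safety board reviews.** Administrative data cannot serve here. The wider count is possible only if the adapted CSRI records why a participant was admitted. The sponsor should confirm that it does, or align the admission item with the ED item for participants still to be followed up. The Trial status section gives 475 consented against a minimum target of 1000, so at least 1000 − 475 = 525 were still to enrol at that point.

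**Cost.** Consent to link health insurance data is optional, so the administrative count covers linked participants only and the denominator must be stated. A change in CSRI wording applies only to later participants, so self-reported counts would mix two definitions and should be shown by version.

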##### Primary and secondary analyses

Baseline descriptive statistics will be generated overall, between treatment groups and between recruitment settings. Employment status and medication use will be described at baseline and 3 months. Prior 3-month health care utilization assessed with the CSRI (and validated with health administrative data when available) will be described at baseline and at 3 months. All primary and secondary outcomes will be described at baseline and 3 months, including the RAS-r and CIQ subscales. In addition, at baseline and 3 months, we will describe the proportion of participants with PHQ-9 and GAD-7 scores of 10 or more, indicative of clinically important levels of depression and anxiety [40], respectively. At 3 months, we will describe clinically important cutoffs on the PHQ-9 and GAD-7 including a reduction of 5 or more points from baseline (clinically meaningful change), reduction in score of 50 % or more from baseline (response), and a score less than 10 (remission) [40]. Adverse event descriptive data will be reported at 3 months, and again at 6 months for the BWW extension group. BWW satisfaction descriptive data will be reported at 3 months for ITG participants and 6 months for DTG participants.

The primary outcome, RAS-r at 3 months, will be analyzed with an intent-to-treat analysis using an ANCOVA controlling for baseline RAS-r score as well as treatment group, unadjusted and adjusted for baseline PHQ-9, baseline GAD-7, age, sex, education, relationship status, household income, duration of episode, and recruitment setting. In sensitivity analysis, we will repeat this using a marginal structural model to account for attrition.

The same analysis will be repeated for all secondary outcomes at 3 months controlling for baseline score and treatment group. Analysis of 3 month data will be completed after all 3 month data have been collected.

In the subset of ITG participants who opt in to the nested extension study, we will examine outcomes at 6 months between treatment groups. Analysis of primary and secondary outcomes will be repeated as described above, controlling for scores at both baseline and 3 months.

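### Death has no listed source that the DSMB will see, and the score-based adverse events count any worsening, however small

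*Protocol article*

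**What the plan says.** The Adverse events section asks the DSMB to look twice, after 150 and after 500 participants have completed 3 months, and to judge whether the trial is safe to continue. It adds: "Health administrative data will not be available within this timeframe and will not be reviewed by the DSMB".

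Table 2 has nine rows. Death is described as "All-cause mortality", with health administrative data as its only measure. Under Recruitment, the route to those data is an optional consent item: "Consent to provide individual provincial health insurance plan (OHIP) number for linkage of survey data to health administrative data (optional". Under Data analysis, they are not analysed until the study ends.

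Three rows are defined by score change without a minimum size: "Increase in PHQ-9 or GAD-7 score over the prior 3 months", "Decrease in CIQ score over the prior 3 months" and "Decrease in EQ-5D-5L scores over the prior 3 months". A fourth uses any rise on PHQ-9 item 9. Primary and secondary analyses does give a size for PHQ-9 and GAD-7, but only for improvement: "a reduction of 5 or more points from baseline (clinically meaningful change". The Adverse events section says that the arms are compared for differences of clinical importance.

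Adverse events are described at 3 months and "again at 6 months for the BWW extension group". Table 1 schedules the same scales and the CSRI at 6 months without restriction by group.

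**The concern.** A body that decides whether a trial may continue needs to hear of deaths. Here the one listed source is closed to it. Every row that the DSMB can see rests on participants' own reports, so someone who has died looks like a non-responder, in a trial that plans for 30% attrition (Power calculation). Recruitment includes ED discharges and a borderline personality disorder clinic, and Table 2 itself tracks suicidal ideation, so the question is not remote.

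The score rows raise a lesser issue. A rise of one point on either of two questionnaires makes a participant an adverse event case. Ordinary variation between two administrations does that often, so the row has low specificity and a real excess of deterioration is harder to see in it.

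Third, the delayed group's only time on BWW is months 4 to 6. The article specifies 6-month adverse event reporting only for the extension comparison.

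**Working it through.** The article states no adverse event rate, threshold or safety power, so there is no figure of the plan's to reproduce.

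**1. What the DSMB can see.** Of nine rows in Table 2:
- One is invisible to it: death.
- Four of the eight visible rows are discrete events from the CSRI or a question added to it: psychiatric hospitalization, mental health ED visit, crisis service use, medication discontinuation.
- One is PHQ-9 item 9.
- Three are score-change rows without a minimum: PHQ-9/GAD-7, CIQ, EQ-5D-5L.

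**2. Deaths.** The article gives no death risk. Assume a 3-month risk m between 0.05% and 0.5%. Expected deaths are n × m, and the chance of at least one is 1 − (1 − m)^n.
- n = 150: 150 × 0.0005 = 0.075, to 150 × 0.005 = 0.75 expected; chance of at least one 7% to 53%.
- n = 500: 0.25 to 2.5 expected; chance of at least one 22% to 92%.

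Through the listed source, the number reaching the DSMB is zero in every case.

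**3. How often an unchanged participant is flagged on PHQ-9 or GAD-7.** All inputs are assumed, in two sets:
- Set A: PHQ-9 mean 13, SD 6; GAD-7 mean 11, SD 5.2; retest correlation r from 0.5 to 0.8; cross-scale correlation 0.65.
- Set B: PHQ-9 mean 14, SD 6; GAD-7 mean 11, SD 5.5; r from 0.6 to 0.84; cross-scale correlation 0.6.

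Hand check for one scale: with no true change, the difference has SD = SD × √(2(1 − r)). For PHQ-9 at r = 0.7 this is 6 × √0.6 = 4.65. Allowing for whole-number scores, P(rise of at least 1) ≈ 1 − Φ(0.5/4.65) = 0.46, and P(rise of at least 5) ≈ 1 − Φ(4.5/4.65) = 0.17. For GAD-7 in set B the SD of the difference is 4.26, giving 0.45 and 0.15.

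Share flagged on either scale, by simulation of 400,000 rounded and bounded score pairs per scenario:

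| Common mean change | Any increase | Increase of at least 5 |
|---|---|---|
| 0 (sets A and B) | about 57–60% | about 13–30% |
| −2 (sets A and B) | about 32–45% | about 4–19% |
| −3 (sets A and B) | about 22–37% | about 2–14% |

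**4. What the flags do to the comparison.** Suppose a share q is flagged in both arms regardless of harm, and BWW truly worsens an extra 5% of its arm, all of whom are flagged. The observable difference is 0.05 × (1 − q).
- Any increase, q = 0.60: 0.05 × 0.40 = 2.0 percentage points.
- At least 5 points, q = 0.13 to 0.30: 0.05 × 0.87 = 4.4 down to 0.05 × 0.70 = 3.5 points.

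The difference shrinks but keeps its sign: dilution, not bias. At the second look (about 333 v 167 at 2:1) the pooled standard error is about 4.6 points for q = 0.60, and about 3.5 to 4.4 points for q = 0.13 to 0.30. At the first look (about 100 v 50) it is about 8.4, and 6.3 to 8.1.

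**5. Delayed group.** At 2:1 and 1000 participants, about 1000/3 = 333 people have their BWW exposure in months 4 to 6.

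**The case against.** A reader might infer that the safety reviews are mostly noise. The documents do not support that. Four of the eight visible rows are discrete events, item 9 is a case where a one-point rise is worth knowing, and nothing says that rows are pooled. A noisy PHQ-9/GAD-7 row therefore does not blur the hospitalization or ED rows.

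A reader might also infer that a 5-point rule would let the DSMB detect a modest harm. Step 4 shows otherwise: an extra 5% is of the order of one standard error at the second look and less at the first. The rule makes the count more meaningful; it does not make the looks powerful.

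The 5-point figure is stated for improvement only, and a sensitive screen for harm is a defensible choice. Mean deterioration is also examined, because PHQ-9, GAD-7, CIQ and EQ-5D-5L are secondary outcomes analysed by ANCOVA at 3 months. This is a fair reason to keep the any-increase count. It does not explain why that should be the only count when the stated aim is differences of clinical importance.

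On death, the article limits the DSMB to available data and points to terms of reference that are not shown; these, or the full protocol, may provide for reporting deaths. One therefore cannot say that the trial has no such route, only that the article's listed source and its DSMB exclusion do not fit together. Nor is a hidden mortality imbalance the right worry: with 0.075 to 2.5 deaths expected, no imbalance could be shown. Individual deaths still matter.

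Finally, the delayed group's months 4 to 6 have no concurrent control, a constraint that the Limitations section explains. That they would never be reported is an inference from silence.

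**Conclusion.** The point holds in two parts of unequal weight.

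The part about death rests on the text alone: the only listed source is withheld from the DSMB, depends on optional consent and is analysed after study end. No death reaches either review through it.

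The part about thresholds is a matter of specificity. Among participants with no true change, about 57 to 60% would be flagged on PHQ-9 or GAD-7, against about 13 to 30% at 5 points. Those figures rest on assumed means, SDs and correlations; general improvement lowers both but leaves the gap. The effect is confined to the score-change rows and weakens a between-arm comparison without biasing it. CIQ and EQ-5D-5L share the missing minimum, but no flag rate was worked out for them.

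The omission of the delayed group's months 4 to 6 is minor. None of this touches the primary analysis. Overall: should-fix, as a cheap improvement.

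**What to change.** 1. **Death.** Add a second source in Table 2: deaths learned through recruiting clinics, follow-up calls or BWW staff, logged in REDCap. Give the DSMB, by arm, the number of deaths and the number not contacted at 3 months, so that silence is visible. Check this against the DSMB terms of reference and reconcile the two.
2. **Score-based rows.** Report an increase of at least 5 points on PHQ-9 or GAD-7 as the main deterioration count. Keep any-increase counts as a supplementary table and leave item 9 as it is. State a minimum change for CIQ and for EQ-5D-5L, naming which EQ-5D-5L score is meant. The article offers no value for either, so the choice needs its own justification. Fix all of these before any unblinded review.
3. **Delayed group, minor.** Add a descriptive 6-month column for its adverse events, labelled as having no concurrent control.

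Cost: an edit to Table 2, one log field and one table column, using existing contacts and data already collected. The downside is a small change to adverse event tabulation after 475 participants have consented, and fewer people flagged in the main count, which the supplementary table covers.
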